## Study aim and objectives

Older people with multimorbidity frequently experience insufficiently coordinated care. Therefore, the project aims to improve the coordination and performance of their cross-sectoral routine health care and address the evidence gap between mono-disease approaches and complex collaborative chronic care in old and very old people with multimorbidity. In this respect, the objective of the trial is to evaluate the effectiveness of local, collaborative, stepped and personalised care management for older people with chronic diseases (LoChro-Care). The programme is designed to improve functional health, depressive symptoms, satisfaction with care, and health resource utilisation.

We hypothesise the following improvements, to be tested in comparison with usual care: (1) LoChro-Care will result in better functional health as defined by greater independence in activities of daily living. (2) LoChro-Care will more effectively reduce depressive symptoms. (3) LoChro-Care will improve satisfaction with care. (4) LoChro-Care will lead to a more appropriate utilisation of health and nursing care services in terms of decreased emergency hospitalisations, reduced non-elective hospital days and nursing home admissions, more adequate use of informal and formal community services and enhanced disease self-management abilities, and will thus contribute to health care cost savings. (5) Positive LoChro-Care effects will occur directly after the 12-month intervention and will be maintained for at least an additional six months after the intervention.

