### Intervention group

LoChro-Care follows the ARIADNE principles for the management of multimorbidity [37]. These are: (1) a thorough assessment of interactions between the patient’s conditions, treatments, constitution, and context; (2) a prioritisation process of multiple health problems that takes into account the patient’s preferences, and (3) individualised management that utilises the best options for care and services. The personalised, stepped, cross-sectoral and collaborative LoChro-Care programme will be provided by a qualified nurse who specialises in health education or a social worker acting as CCM. They will be backed up by an interdisciplinary geriatric team, which will provide bi-monthly supervision and can be contacted in the case of urgent need for action. LoChro-Care will be initiated directly after the patients’ discharge from inpatient treatment and includes seven to 16 contacts within a 12-month period.

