#### LoChro-care: Key agents and core elements

Novel aspects of LoChro-Care are reflected in the combination of the following approaches within one connected concept: (1) enhancing self-management based on stepped care plans delivered in plain language, which are understandable and foster easy communication between the patients or caregivers and service providers, (2) facilitating the appropriate use of informal support and the use of lay helpers if necessary, (3) supporting the CCM through an interdisciplinary geriatric team, (4) providing the CCM with selected online information on local geriatric services and (5) evaluating the stepped care plans and the spectrum of local geriatric services in its entirety to generate a best practice guideline for regional stepped collaborative care.

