Cost-effectiveness analyses of LoChro-Care will be carried out from the healthcare perspective. Therefore, the change-from-baseline scores of the WHODAS, PHQ-9 and PACIC will be analysed in relation to the costs of medical resource utilisation and the costs of the work of chronic care managers. Incremental cost-effectiveness ratios and corresponding confidence intervals will be estimated using seemingly unrelated regressions, a multivariate regression technique that accounts for the potential correlation between cost and outcome (score) measurements. Based on data from the FIMA instrument, standardised unit costs will be applied to quantify the costs of medical resource utilisation. With the aim of increasing the precision of the assessment, we will complement the FIMA questionnaire with a prospective diary method in a subsample. Over a 12-month period, patients will be requested to record their medical resource utilisation. The diary is designed as a table including the main aspects of medical costs. Cost-effectiveness analyses will be conducted for the whole sample as well as for the subsample with diary cost assessments in the intervention and control group. In addition, the costs of the work of chronic care managers will be determined. We will consider employers’ labour costs and costs for the administration and coordination of the chronic care managers (lump sum of 25% of personnel costs).

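### The stated cost rule has no line for the geriatric team, which lowers cost in the LoChro-Care arm only unless the 25% lump sum covers it; the ICER, the only summary named, is unreadable when negative

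*Protocol article*

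**What the plan says.** All references are to the Protocol article.

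**Cost side (Statistical analyses).** "Cost-effectiveness analyses of LoChro-Care will be carried out from the healthcare perspective". Outcome changes on WHODAS, PHQ-9 and PACIC are set against "the costs of medical resource utilisation and the costs of the work of chronic care managers". Medical use is priced with standard unit costs from the FIMA questionnaire, supplemented by a patient diary in a subsample. CCM work is priced as labour at employer cost plus "costs for the administration and coordination of the chronic care managers (lump sum of 25% of personnel costs".

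**What the intervention contains.** The section on key agents and core elements lists "supporting the CCM through an interdisciplinary geriatric team" as the third of five elements. The Intervention group section describes a team "which will provide bi-monthly supervision and can be contacted in the case of urgent need for action". The section on implementation and time schedule adds regular counselling of the CCM by a geriatrician and by a study team member from the University of Education, introduced as a means of securing treatment fidelity.

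**Summary measure (Statistical analyses).** "Incremental cost-effectiveness ratios and corresponding confidence intervals will be estimated using seemingly unrelated regressions". No other summary is named. In Study aim and objectives, hypotheses 1 to 3 predict better function, fewer depressive symptoms and more satisfaction with care; hypothesis 4 predicts more appropriate service use that "will thus contribute to health care cost savings".

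**The concern.** A cost-effectiveness result is only as fair as its list of costs. Here the list is written down, and a named core element of the programme does not appear on it. Clinical supervision and urgent consultation are healthcare resources under the perspective the article chooses. The Discussion envisages bringing CCM interventions into usual care, so a payer adopting the programme would meet this cost. If it is left out, only one arm looks cheaper than it is.

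The second issue concerns reading the result. A ratio of two differences loses the sign of each. If LoChro-Care proved both better and cheaper, the ICER would be negative, and a negative value alone does not show which of two opposite results has occurred. If the effect estimate is not clearly different from zero, the interval for the ratio may have no finite limits.

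**Working it through.** **1. The plan's own figures.** The 25% lump sum has no derivation to reproduce. The sample size, used in step 5, does reproduce. With a standardised difference of 0.3, one-sided 5% level and 95% power, the noncentral t distribution gives power 0.9499 at 241 and 0.9506 at 242 per arm, so 242 is right. Dropout: 242 / 0.8 = 302.5, rounded up to 303 per arm, and 2 × 303 = 606.

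**2. Can another cost line recover the team's time?**
- FIMA and the diary record the patient's own use of services. Supervision is given to the CCM, so patients cannot report it.
- The Control group section describes usual discharge management and no CCM, so there is no matching input to cancel it.
- The lump sum is worded as administering and coordinating CCMs. It does not mention clinical supervision or consultation.

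So on the plain wording any omission falls on the intervention arm alone, and its direction is known.

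**3. Size, over an assumed range.** Let L be CCM labour cost and S the team input. Reading the 25% as a share of L, the counted programme cost is 1.25 L and the full cost is 1.25 L + S. The share missed is S / (1.25 L + S). The article gives no hours, wages or caseload, so S is assumed:

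| S as share of L | Full cost | Share missed |
|---|---|---|
| 5% | 1.30 L | 3.8% |
| 10% | 1.35 L | 7.4% |
| 20% | 1.45 L | 13.8% |
| 30% | 1.55 L | 19.4% |
| 50% | 1.75 L | 28.6% |

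These are shares of programme cost. Incremental cost also contains the between-arm difference in medical use; it is understated by S in absolute terms. The sign of net cost changes only if service savings per patient lie between 1.25 L and 1.25 L + S. For example, with savings of 1.4 L and S = 0.2 L, the counted net cost is 1.25 L − 1.4 L = −0.15 L and the full net cost is 1.45 L − 1.4 L = +0.05 L.

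**4. A negative ratio.** Illustrative differences, effect coded so that positive means benefit:
- saves 300, gains 3: −300 / 3 = −100
- costs 300 more, loses 3: 300 / −3 = −100
- saves 300, gains 1: −300 / 1 = −300
- saves 300, gains 6: −300 / 6 = −50

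The first two are opposite conclusions with the same ratio. In the last two, the better result has the ratio nearer zero. Net benefit, λ × effect − cost with willingness to pay λ, separates the first pair at any positive λ: 3λ + 300 is positive and −3λ − 300 is negative.

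**5. The interval.** A 95% Fieller interval is bounded only when the effect differs from zero at the two-sided 5% level. With 242 per arm and an unadjusted comparison, z = SMD × √(242/2) = 11 × SMD, and the chance of a bounded interval is Φ(z − 1.96) + Φ(−z − 1.96):
- SMD 0.3: z = 3.3, chance 0.91
- SMD 0.2: z = 2.2, chance 0.60
- SMD 0.1: z = 1.1, chance 0.20

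**The case against.** The strongest reply on costing is that the article nowhere says team time is excluded. The 25% may be meant to cover some or all of it, and counselling introduced for treatment fidelity can be read as trial quality assurance, which need not be a programme cost. Both points stand. They make the size unknown and leave the sponsor a simple way to close the gap. They do not remove the gap, because the lump sum's wording does not reach clinical supervision or urgent back-up, and the fidelity remark is attached to the counselling, not to the team's bi-monthly supervision.

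On the ratio, the reply is that seemingly unrelated regressions estimate both differences jointly, that the article does not say the ratio will stand alone, and that net benefit and acceptability curves are commonly left to a fuller plan. This also stands: their absence is not an error.

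A reader might go further and infer that the protocol predicts net savings with benefit, so that a negative ICER is the expected result. The text does not support this. Hypothesis 4 speaks of a contribution to savings and does not say they exceed the cost of the programme. If net cost is positive and outcomes improve, the ICER can be read normally. Nor is an unbounded interval the expected outcome: at the design effect of 0.3 the interval would be bounded about nine times in ten.

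**Conclusion.** The point holds as a costing rule with a known direction of bias and an unknown size. As written, the rule leaves geriatric team time without a cost line, and this can only favour LoChro-Care, unless the sponsor intends the lump sum to cover it. The range of about 4% to 29% of programme cost rests entirely on the assumption that team input is 5% to 50% of CCM labour. A reader might conclude that cost-effectiveness is materially flattered; without hours or wages, the documents cannot show that.

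The ICER issue is secondary and conditional. It arises if service savings exceed programme cost, which is possible under hypothesis 4 but not certain, or if the effect is smaller than planned (chance of a bounded interval 0.60 at 0.2 SD). The probabilities assume 242 per arm, no gain from covariate adjustment, and the same standardised effect on whichever scale enters the ratio.

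Neither issue touches the primary composite, the sample size or the test of effectiveness. It is worth fixing because it affects the economic conclusion and costs little.

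**What to change.** **Costing.** Keep a log of the geriatric team's supervision and consultation hours and add them to intervention cost at employer cost. Alternatively, state that the 25% lump sum covers this time and test that in a sensitivity analysis over a range of team input. Time spent purely on trial fidelity may be left out if it is identified as such.

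**Reporting.** From the seemingly unrelated regressions already planned, report incremental cost, incremental effect and incremental net benefit over a range of willingness-to-pay values, alongside any ICER. Code every effect so that positive means benefit; for PHQ-9 the hoped-for change is a fall, so the sign has to be fixed in advance.

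**Cost of the change.** A short time log, a few more outputs from the same model, and a somewhat higher stated intervention cost. The Trial status section describes recruitment as ongoing in February 2019; hours are easier to record as they occur than to reconstruct, and any period already past would need an estimate labelled as one.

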### Ethical considerations and safety

#### Good clinical practice

The treatment plan and intervention techniques are compliant with recommendations of current national and international clinical guidelines. Control group patients will receive full usual care management according to ethical and legal standards as established in Germany. Experimental group patients will receive an add-on coordination without any additional risk and without any restriction of the usual care management. There is no evidence suggesting that care management increases the risk of morbidity, mortality or functional decline. If adverse events occur during the trial, they will be documented by the CCM or, for patients in the control group, by the data management team. However, there is no indication from studies that older people with multimorbidity are exposed to a higher risk of adverse events when participating in chronic care management programmes. Furthermore, the LoChro-Care study is a sponsor-driven trial without any commercial interest of the involved researchers, clinical staff or participants, and a scientific and practice advisory board has been initiated. Given these facts, in our judgement, the scientific and practice advisory board will sufficiently ensure quality and there is no need for specific committees on data monitoring and safety. All study materials and procedures will (1) be discussed a priori with the patient representatives of our practice advisory board, (2) adapted according to their feedback, (3) piloted with eligible patients, (4) again adapted to patients’ needs and (5) finally approved by our practice and scientific advisory board. The ethical committee of the University of Freiburg has reviewed our proposal regarding conformity with current ethical standards for participants’ safety and confidentiality and has given formal ethical approval (no. 495–17, date: 19th December 2017). All relevant protocol modifications and amendments will be submitted to the responsible ethical review boards and will be reported within the scope of the publication of the trial findings. Written informed consent is mandatory for each patient for enrolment in the study.

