**Methods:**

The study will evaluate the effects of LoChro-Care on functional health, depressive symptoms and satisfaction with care, resource utilisation as well as health costs in older persons with long-term conditions. The trial will compare the effectiveness of LoChro-Care and usual care in a cross-sectoral setting from hospital to community care. We will recruit 606 older adults (65+) admitted to local hospital inpatient or outpatient departments who are at risk of loss of independence. Half of them will be randomised to receive the LoChro-Care intervention, comprising seven to 16 contacts with chronic care managers (CCM) within 12 months. The hypothesis that LoChro-Care will result in better patient-centred outcomes will be tested through mixed-method process and outcome evaluation and valid measures completed at baseline and at 12 and 18 months. Cost-effectiveness analyses from the healthcare perspective will include incremental cost-effectiveness ratios.

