## Methods/design

### Trial design/setting

The present study will be conducted within the routine care context and is designed as a prospective, two-group usual care controlled trial with 1:1 randomisation on the participant level. Participants will be recruited from all for geriatric patients relevant inpatient and outpatient units of the Medical Center – University of Freiburg, especially the emergency unit. During the 18-month observation period, the chosen endpoints will be measured three times (at baseline, after 12 months and after 18 months). Participants in the intervention group will be supported by a chronic care manager (CCM) over a period of 12 months. The study will be implemented according to CONSORT guidelines (see Fig. 1).

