#### Assessment

The chosen endpoints will be measured at baseline and at 12 and 18 months using valid and reliable outcome assessment instruments as described above. We chose feasible and brief patient-reported outcomes in order to evaluate the participants’ perspective and to motivate the patients to become involved through self-reflection and feedback. If necessary, proxy versions of particular/single assessment instruments for caregivers will be used to avoid missing data, e.g. in persons with severe dementia. For proxy assessment, we will only use those instruments which do not require introspection and can thus be rated by caregivers. Additionally, the medication regimens for all enrolled patients will be recorded at baseline and at both follow-up time points.

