#### Assignment and randomisation

After obtaining written consent from participating patients, external assessors responsible for the screening will send contact details of the patient, relatives as well as the baseline assessment to the primary coordinating centre. There, the allocation of the patients to the study arms will be performed. Participating patients will receive a pseudonymised code and will then be assigned to the intervention or control group according to a computer-generated randomisation schedule by a study coordinator not involved in assessment or intervention procedures. Block randomisation will be used with no stratification. After assignment to the intervention or control group, the pseudonymised patient identifiers and the baseline assessment will be sent to the study centres responsible for the data management. The study site responsible for the implementation of the intervention will receive names and contact details of the patients in the intervention group in order to begin the intervention process.

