#### Blinding

In both groups, patient outcomes will be collected by independent assessors to prevent the contamination of the CCM by patient assessment. Due to the pseudonymisation process, the statistician will analyse the primary and secondary outcome data without knowledge of the subjects’ allocation to the study arms. For additional qualitative analysis of CCM data in the experimental group, this kind of blinding is not possible. Due to the nature of the intervention, participants and CCM will not be blinded to the type of intervention.

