#### Quality control of data

The research group will ensure data quality by following standard operating procedures (SOPs). The assessors will directly document LoChro-Care data in pseudonymised source data Case Report Forms (CRFs). Data will be checked for completeness, plausibility and incorrect data, which will lead to queries by the study site responsible for data management. If queries lead to data correction, this will be done by the assessors (source data CRFs) and the data management centre. The uniformity of corrections made at the data management centre will be checked during onsite monitoring visits. This procedure ensures source data verification. In order to ensure efficient and reliable monitoring and data management processes, the following SOPs of the “Technology, Methods, and Infrastructure for Networked Medical Research” (Technologie- und Methodenplattform für die vernetzte medizinische Forschung, TMF) will be adapted to specific requirements of the LoChro-Care study: (1) SOP monitoring visit: to ensure the reliable evaluation of identical corrections due to queries and the uniformity of data in the patient file at the study site and the data provided in the sociodemographic assessment. (2) SOP data check: to ensure identical procedures when incoming data are checked for correctness and queries are handled. (3) SOP data entry check: to ensure a rate of data entry errors of less than 0.2%. (4) SOP adverse event: to ensure that adverse events are disclosed early and handled appropriately.

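### Adverse events are documented by different people with very unequal patient contact in the two arms, so any by-arm count would reflect ascertainment as well as risk

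*Protocol article*

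**What the plan says.** The rule is in the protocol article under Good clinical practice. If adverse events occur, "they will be documented by the CCM or, for patients in the control group, by the data management team". The same section states that no separate data monitoring or safety committee is needed.

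The amount of contact in each arm follows from other sections:

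- **Intervention arm.** The Abstract describes the programme as "comprising seven to 16 contacts with chronic care managers (CCM) within 12 months", and the Intervention group section gives the same range. The Blinding section says that the CCM is not blinded.
- **Both arms.** Under Assessment: "The chosen endpoints will be measured at baseline and at 12 and 18 months". Under Blinding: "In both groups, patient outcomes will be collected by independent assessors". These assessors are not named as recorders of adverse events.
- **Data management.** Under Assignment and randomisation, after allocation "the pseudonymised patient identifiers and the baseline assessment will be sent to the study centres responsible for the data management". No patient contact by this team is described. The Data protection section does not list data management among the centres that can link names to pseudonyms.

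Under Quality control of data, a standard operating procedure (SOP) for adverse events is listed, with the aim "to ensure that adverse events are disclosed early and handled appropriately".

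**The concern.** Who records an event, and how often that person hears from the patient, depends on the allocated arm. The intervention-arm recorder delivers the programme and speaks with the patient repeatedly during the year. The control-arm recorder is a data team, and the patients concerned have no scheduled study contact between baseline and month 12. This is a stated rule, and nothing else in the article evens it out.

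At stake is the meaning of any adverse event table split by arm. More contact would tend to raise the intervention-arm count. An unblinded recorder who delivers the programme might also attribute or report less. A reader of such a table could not separate either effect from a true difference, so it would neither reassure nor warn.

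A second, smaller point is that the SOP aims at early disclosure, yet the described schedule gives control patients no contact before month 12 that would serve it.

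**Working it through.** The article gives no adverse event figure to reproduce. The check is a count of contacts, followed by an illustration.

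**1. The contact range.** From the section on implementation and time schedule:

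- Standard contacts: a first visit, a care-plan discussion, a monitoring visit, three telephone calls and a closing visit, which makes 7.
- Additional contacts: 6 for depression and 3 for diabetes.
- Maximum: 7 + 6 + 3 = 16. The stated range of 7 to 16 is reproduced.

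**2. Scheduled contacts after baseline.**

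| Period | Intervention | Control |
|---|---|---|
| Up to and including month 12 | 7 to 16, plus T1 = 8 to 17 | 1 (T1) |
| Whole 18 months | 7 to 16, plus T1 and T2 = 9 to 18 | 2 (T1, T2) |

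T1 and T2 are counted as occasions in both arms. This is generous to the control arm, because the article does not say that assessors pass events on.

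**3. What this could do to counts when true rates are equal.** An event can be picked up only at contacts that follow it. Assumptions, none of them from the article unless stated:

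- event times are uniform over 78 weeks, with T1 at week 52 and T2 at week 78;
- there are seven CCM contacts, at weeks 1, 3, 7, 18, 29, 40 and 50.5. The first three and the last follow the described schedule; the telephone dates are assumed, because the session figure is not shown;
- each later contact detects the event independently with probability p.

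Contacts remaining, by time of event:

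| Event in weeks | Length (weeks) | Intervention | Control |
|---|---|---|---|
| 0–1 | 1 | 9 | 2 |
| 1–3 | 2 | 8 | 2 |
| 3–7 | 4 | 7 | 2 |
| 7–18 | 11 | 6 | 2 |
| 18–29 | 11 | 5 | 2 |
| 29–40 | 11 | 4 | 2 |
| 40–50.5 | 10.5 | 3 | 2 |
| 50.5–52 | 1.5 | 2 | 2 |
| 52–78 | 26 | 1 | 1 |

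Mean contacts remaining:

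- Intervention: (9 + 16 + 28 + 66 + 55 + 44 + 31.5 + 3 + 26)/78 = 278.5/78 = 3.6.
- Control: (104 + 26)/78 = 1.7.

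Proportion captured = Σ (length/78) × [1 − (1 − p)^k], where k is the number of contacts remaining. For control at p = 0.1 this is (52 × 0.19 + 26 × 0.10)/78 = 0.160.

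| p | Intervention | Control | Apparent ratio |
|---|---|---|---|
| 0.1 | 0.295 | 0.160 | 1.84 |
| 0.3 | 0.631 | 0.440 | 1.43 |
| 0.7 | 0.893 | 0.840 | 1.06 |
| 0.9 | 0.966 | 0.960 | 1.01 |

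Seven contacts is the lower end of the range. More contacts would widen the gap where p is low.

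**4. Direction.** If only a fraction r of the intervention-arm events that come to light is written down, the ratio is multiplied by r. It falls below 1 when r is below 0.160/0.295 = 0.54 (p = 0.1) or 0.440/0.631 = 0.70 (p = 0.3). The article gives no basis for choosing r.

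**The case against.** The strongest reply is that nothing planned rests on this comparison. The hypotheses, the outcome table and the statistical analyses contain no adverse event endpoint or between-arm test, and the SOP treats events as something to handle. That stands: the point applies to a by-arm report if one is made, not to a specified analysis.

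Four stronger readings are tempting, and the article does not support them.

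- **That adverse event records are the trial's only safety evidence.** FIMA, WHODAS and PHQ-9 are collected at baseline, 12 and 18 months in both arms. Emergency hospitalisations, non-elective hospital days and nursing home admissions are named in the fourth hypothesis. FIMA is not, however, designated as a safety source, and it measures service use rather than events in general.
- **That the trial's statement of no additional risk depends on this contrast.** The supporting sentences appeal to earlier studies, not to this trial's counts.
- **That control-arm events cannot be disclosed early.** The article says who documents events, not every route by which they may be reported. The SOP is not shown, and a subsample that includes control patients keeps a 12-month resource-use diary. What can be said is that no scheduled contact before month 12 serves that aim.
- **That the gap in contacts, 9 to 18 against 2, translates directly into counts.** With p = 0.1, giving every event all nine occasions yields 1 − 0.9^9 = 0.61 against 1 − 0.9^2 = 0.19, a ratio of 3.2. That credits events with contacts that took place before they happened.

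The different recorders remain. Naming them is a rule the article states, so it cannot be put down to condensation.

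**Conclusion.** The point holds in a limited form. By-arm adverse event counts collected under this rule would have unequal ascertainment, and the article fixes neither its size nor its direction. Under the assumptions above, equal true rates would appear as a ratio of about 1.4 to 1.8 for events with low detection per contact. The ratio would be close to 1 for events that almost always come to light, as deaths might. Under-reporting by the unblinded CCM could cancel or reverse it. The detection probabilities, the event-time distribution and the telephone dates are assumptions; the contact counts come from the article.

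A reader might infer that the trial's results are biased more widely. They are not affected by this rule: the primary and secondary outcomes are collected by independent assessors on the same schedule in both arms. The change is worth making because it is cheap and no data monitoring or safety committee is planned.

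**What to change.** - Have the independent assessors ask one fixed event list, with the same wording and recall window, at T1 and T2 in both arms. Suitable items are death (from a proxy or records), unplanned admission, nursing home entry, falls and other serious events.
- Supplement this with the FIMA data on hospital and nursing home use, which are already symmetric.
- State that any between-arm safety table draws on these sources only.
- Keep CCM-reported events as a separate listing, used for handling and not for comparison.
- Reconcile the SOP's aim of early disclosure with the control-arm schedule. Questions at T1 and T2 make the comparison fair but do not by themselves bring control-arm events to light before month 12.

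The cost is a few questions at visits already planned, with assessors already in place, plus an edit to the SOP. Treatment, visit schedule and sample size do not change. The downside is that some minor events will not be recalled at 12 or 18 months, but on the same schedule in both arms.
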